#### Trial design

The trial has been designed as a randomized double-blind placebo-controlled multicentre trial to evaluate the safety and efficacy of HCQ to prevent and/or minimize SARS-CoV-2 infection during pregnancy. A total of 714 pregnant women are expected to participate in the study (see sample size calculation).

The study participants will be stratified by clinical presentation and SARS-CoV-2 PCR results. The following are the study groups:

- **SARS-CoV-2-PCR confirmed, infected** pregnant women:
  - a. *symptomatic* (n=100)
  - b. *asymptomatic* (n=100)
- **SARS-CoV-2 PCR negative** pregnant women in **contact** with a SARS-CoV-2-infected confirmed or suspected case (n=514).

Women in each group will be randomly allocated to receive either HCQ or placebo. Evaluations will include safety and tolerability, SARS-CoV-2 PCR and COVID-19 clinical diagnosis and presentation, as well as neonatal SARS-CoV-2 by PCR and IgM/IgG.

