#### **Sample size**

A sample size of 100 infected pregnant women of each asymptomatic and symptomatic group, 1:1 randomly allocated into two study arms, allows to detect an effect size of 30%, 34% and 39% with 80% power and two-tail type-I error of 0.05 assuming 3%, 10% and 30% curation rates in the control group, respectively. In other words, this sample allows detecting differences if the cure rates in the intervention group are at least 33%, 44%, and 69%, respectively. A sample size of 257 non-infected, contact positive, pregnant women per intervention arm will be needed to detect a 3 % reduction in the prevalence of infection with 80% power and two-tail type-I error of 0.05, assuming a prevalence of infection in the control group of 3% after two weeks of follow up.

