#### **b) Treatment arm allocation**

Participants will be then randomized in a 1:1 ratio to HCQ (400 mg/day for three days, followed by 200 mg/day for 11 days) or placebo (2 tablets for three days, followed by one tablet for 11 days).

Allocation of participants to study arms will be done centrally by the trial's Sponsor (the Barcelona Institute for Global Health, ISGlobal) by block randomization. This method will ensure balanced allocation to both arms. The electronic CRF will assign automatically a study number to each participant, depending on her study group and recruitment site. Each number will be related to a treatment number, which assigns them to one of the study arms. Randomizations lists with treatment assignment for each study participant will be concealed in opaque sealed envelopes and only open in case of urgent need following study unblinding procedures.

A study card will be given to the participant in order to facilitate their clinical management in case they attend primary care centres or other hospitals.

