#### **Statistical models and methods of analysis**

The primary analysis of the trial will be:

- The comparison of the proportion of negative SARS-CoV-2 PCR at day 14 after initiating treatment administration among those women who were SARS-CoV-2 PCR positive at recruitment in the ITT and ATP cohorts.
- The comparison of the proportion of pregnant women who were negative SARS-CoV-2 PCR at recruitment and close contacts of confirmed cases of SARS-CoV-2 infection, with a positive PCR for the infection at day 14, in the ITT and ATP cohorts.

Proportions will be compared between the two intervention-arms within each group using the Fisher exact test and presented as relative risk ratio (RR) or reduction of the RR ( $1 - RR * 100\%$ ) if RR lower than 1. Adjustment for co-variables and possible confounders will be done using Poisson regression with a log link and robust estimate of the covariance (Huber method), using the method proposed by Zou et al. 2014 and 2013.

Continuous variables will be compared between groups using Wilcoxon rank sum test and the effect presented as Mean Difference. Adjustment for co-variables and possible cofounders will be done using ordinary least square regression. Variables will be transformed to the logarithm scale if normality is improved and results presented as Proportional Difference. If after transformation, non-normality of the residuals is detected using diagnostic regression plots, robust intervals of confidence and Wald test will be presented instead.

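### Contact-group primary test: Fisher's exact test is valid but conservative, and a pre-specified unconditional exact test would add 8 to 12 points of power with the same 514 women

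*Protocol*

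**What the plan says.** Under Statistical models and methods of analysis, the two arms of each study group are to be compared "using the Fisher exact test and presented as relative risk ratio (RR"). A Poisson model with robust variance is reserved for covariate adjustment. The test is therefore fixed in the protocol itself and not left to a later document.

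The Sample size section says that "257 non-infected, contact positive, pregnant women per intervention arm will be needed to detect a 3 % reduction in the prevalence of infection". Power is set at 80% and the two-sided error at 5%, and the control arm is taken to have a 3% infection rate. A 3-point reduction from 3% is 3% v 0%. Allocation is 1:1, and the Trial design section gives the contact group 514 women in total, which is 2 × 257.

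**The concern.** Fisher's test conditions on the total number of infections. The arm sizes are fixed by design, but that total is not. When it is small, the conditional distribution has few possible values, and the attainable significance levels jump well past 5% or fall well short of it. Only 257 × 0.03 = 7.7 infections are expected in the control arm, so moving the cut-off by one infection changes the power appreciably.

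At stake is power in the largest part of the trial (514 of 714 women). The planning effect there is complete elimination of infection. Any smaller benefit leaves the test further below 80%, so conservatism that can be avoided at no cost in patients is worth removing.

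**Working it through.** **Inputs.** 257 per arm, 3% control rate, 3-point reduction, two-sided 5% and 80% power (Sample size); 1:1 allocation (Treatment arm allocation); Fisher's exact test (Statistical models and methods of analysis). HCQ-arm rates of 0.25%, 0.5% and 1% are my assumptions, to show less than complete protection.

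**1. Reproduce the 257.** Pooled normal approximation without continuity correction:

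n = [1.960·√(2·p̄·(1−p̄)) + 0.842·√(p₁(1−p₁) + p₂(1−p₂))]² / (p₁−p₂)²

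With p₁ = 0.03, p₂ = 0 and p̄ = 0.015: [1.960·√0.02955 + 0.842·√0.0291]² / 0.0009 = (0.3369 + 0.1436)² / 0.0009 = 256.5, so 257. Power by the same formula is 80.1%. The stated figure is reproduced, but from the large-sample formula and not from Fisher's test.

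**2. Fisher's cut-off and power.** With no infections on HCQ and k on placebo, the two-sided p-value is 2·C(257,k)/C(514,k). It is 0.061 for k = 5 and 0.030 for k = 6, so six are needed. Power at 3% v 0% is P(X ≥ 6) for X ~ Bin(257, 0.03), which is 78.5%.

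**3. Fisher's true size.** Binomial probabilities summed over all 258 × 258 tables with p ≤ 0.05, both arms at the same rate: 0.9% at a rate of 1%, 1.7% at 1.5%, 2.1% at 2%, 2.6% at 3%.

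**4. Unconditional alternative.** Boschloo's test orders tables by the Fisher p-value. The p-value of a table is then the largest null probability, over the unknown common rate, of a table at least as extreme. The Berger-Boos restriction limits that search to a 99.9% Clopper-Pearson interval for the common rate and adds gamma = 0.001 to the result. Size is 2.5% at a rate of 1%, 3.5% at 1.5%, 3.8% at 2% and 3.8% at 3%. The maximum over the whole range of rates is 4.87%, so the 5% limit holds.

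| Infections (HCQ v placebo) | Fisher p | Boschloo with Berger-Boos p |
|---|---|---|
| 0 v 5 | 0.061 | 0.037 |
| 1 v 7 | 0.068 | 0.040 |
| 2 v 9 | 0.063 | 0.042 |
| 3 v 11 | 0.054 | 0.034 |

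**5. Power, 257 per arm.**

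| Placebo v HCQ rate | Fisher | Boschloo with Berger-Boos | Gain (points) |
|---|---|---|---|
| 3% v 0% | 78.5% | 88.6% | 10.1 |
| 3% v 0.25% | 61.3% | 73.0% | 11.7 |
| 3% v 0.5% | 46.4% | 57.8% | 11.4 |
| 3% v 1% | 24.8% | 33.0% | 8.2 |

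The 88.6% is P(X ≥ 5) under Bin(257, 0.03): the gain at 3% v 0% comes from needing one infection fewer. Fisher would need about 300 per arm to reach it, or 2 × 43 = 86 more women.

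**6. Dependence on the variant.** Plain Boschloo, maximised over all rates, gives p = 0.052 at 0 v 5, so its power at 3% v 0% is also 78.5% and it gains nothing there. An unconditional pooled-Z test rejects at 0 v 4 (p = 0.047) and reaches 95.1%, with maximum size 4.96%.

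**7. Infected groups, 50 per arm, at the protocol's own effects.** Cure rates, Fisher v plain Boschloo: 3% v 33%, 98.3% v 98.9%; 10% v 44%, 97.0% v 97.7%; 30% v 69%, 97.3% v 97.6%. The gain is 0.3 to 0.8 points.

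**The case against.** Fisher's test is valid and standard, and its 78.5% is within two points of the stated 80%. Nothing is stated wrongly, so preferring a more powerful test is optimisation. That stands as a description: a reader might infer that the 257 or the 80% is wrong, and the calculation does not support that. It does not dispose of the point, because the protocol fixes the test and a better valid one is available for a sentence of text.

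A reader might also infer that every primary comparison loses power. At the effects the Sample size section plans for the infected groups, Fisher already has 97% to 98% power and the alternative adds less than a point. The point is confined to the contact group.

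Nor does any unconditional exact test deliver the gain. It runs from nothing to 16.6 points at 3% v 0%, depending on the variant, so a choice made after seeing data would be open to selection. This stands, and the fix has to meet it.

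Finally, Fisher's test rests on the random allocation, whereas the unconditional test assumes one binomial rate per arm. Numbers are assigned by study group and site across five hospitals, so a common rate is an approximation. This is a fair caveat but a modest one, since the Fisher comparison as planned ignores site as well.

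**Conclusion.** The point holds for the contact group as an efficiency loss. At the planned 3% rate Fisher's test runs at about half the allowed 5%. A named unconditional exact test that still respects 5% gains 8 to 12 points for HCQ-arm rates from 0% to 1%.

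These figures assume that all 514 women are analysed, a 3% control rate, and a common rate within each arm. The change does not rescue the design against modest effects: at 3% v 1% the preferred test still has only 33% power. It is a cheap improvement worth making, not a correction of an error.

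**What to change.** In Statistical models and methods of analysis, for the contact-group primary comparison only, replace Fisher's exact test with wording such as: Boschloo's unconditional exact test at two-sided 5%, with the Berger-Boos restriction of the common infection rate (gamma = 0.001); Fisher's exact test will be reported as a sensitivity analysis. Fix both the variant and gamma before unblinding. Fisher can stay for the infected groups.

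The change concerns the test only. If a matching confidence interval is wanted, name its statistic, state that it is on the relative-risk scale the protocol reports, and say how zero infections in one arm are handled, since the log relative risk then has no finite estimate.

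Cost: one sentence and no extra patients or data. Downsides: a less familiar test, one tuning constant, software that must support the restriction (not every routine for Boschloo's test does), and reliance on a common rate per arm across five sites.

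### The contact group is sized on no infections under HCQ, and with an empty HCQ arm the named covariate-adjustment model has no finite estimate and gives a meaningless interval and p-value

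*Protocol*

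**What the plan says.** Protocol section 5.a, Sample size, asks for this contact group: "A sample size of 257 non-infected, contact positive, pregnant women per intervention arm". The stated aim is to "detect a 3 % reduction in the prevalence of infection". Power is set at 80% with a two-sided 5% level, and the control arm is taken to reach 3% infected by two weeks. Allocation is 1:1 (section 5.c, Treatment arm allocation).

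Protocol section 5.i, Statistical models and methods of analysis, compares proportions between arms "within each group using the Fisher exact test". Results are "presented as relative risk ratio (RR) or reduction of the RR" where the RR is below 1. On covariate adjustment, the section says that it "will be done using Poisson regression with a log link and robust estimate of the covariance (Huber method"). The section makes no provision for an arm with no events.

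**The concern.** Taking 3 points off a control rate of 3% leaves 0%, so the alternative for which this group is powered is an HCQ arm with no infections. A Poisson model with a log link estimates the logarithm of the relative risk, and the logarithm of zero is not finite. One might expect the software to stop, or to print a huge standard error that warns the analyst. The robust covariance named in the protocol does the reverse: the standard error stays small while the coefficient runs away, and the output looks like overwhelming evidence.

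At stake is the adjusted result for the prevention question. It could sit beside a Fisher test that says something quite different. Without a rule, the choice between the two, or of a third method, would be made after the data are seen.

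**Working it through.** **Inputs.** From the protocol: n = 257 per arm, control rate 3%, reduction 3 points, two-sided alpha 0.05, power 80%, Fisher test, RR, and log-link Poisson with Huber covariance. All calculations assume that every woman has an outcome.

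**1. Reproduce 257.** With pooled variance and no continuity correction, p1 = 0.03, p2 = 0 and mean 0.015:

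n = [1.96 × sqrt(2 × 0.015 × 0.985) + 0.842 × sqrt(0.03 × 0.97)]² / 0.03² = (0.3369 + 0.1436)² / 0.0009 = 256.5, rounded up to 257.

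At 3% v 0.1% the same formula needs 284. The stated figure therefore belongs to 3% v 0%. The expected count is 257 × 0.03 = 7.7 infections against 0.

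**2. Why the robust standard error stays small.** In a model with treatment only, let a be the number of control events. The robust variance of the log rate is 1/a - 1/257 in the control arm. In the empty arm the fitted mean m tends to 0, each residual is -m, and the robust variance is 257m² / (257m)² = 1/257. The sum is 1/a, so SE = sqrt(1/a) however far the coefficient has drifted.

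**3. Fits at 257 per arm** (statsmodels Poisson GLM, HC0 covariance, default tolerance; each fit reports convergence):

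| Control v HCQ events | Coefficient | Robust SE | Robust p | Fisher p |
|---|---|---|---|---|
| 1 v 0 | -20.4 | 1.00 | 2e-92 | 1.0 |
| 3 v 0 | -21.4 | 0.58 | 2e-300 | 0.25 |
| 5 v 0 | -21.4 | 0.45 | prints as 0 | 0.061 |
| 6 v 0 | -22.4 | 0.41 | prints as 0 | 0.030 |
| 8 v 0 | -22.4 | 0.354 | prints as 0 | 0.0074 |
| 8 v 1 | -2.08 | 1.06 | 0.049 | 0.037 |

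- For 8 v 0 the printed 95% interval for the RR is about 1e-10 to 4e-10.
- Model-based errors would expose the failure: for 1 v 0 the SE is about 16,000 and p = 0.999.
- The printed values depend on the convergence tolerance. For 1 v 0, p is 5e-30 at 1e-4, 2e-92 at 1e-8 and 8e-190 at 1e-12.
- Adding a random covariate to 1 v 0 still gives p = 1e-93.
- With one HCQ event (8 v 1) the model behaves normally.

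**4. How often the two analyses disagree at 3% v 0%.** Fisher against an empty arm is non-significant at 5 or fewer control events (p at least 0.061). With X ~ Bin(257, 0.03), P(X ≤ 5) = 21.5%. Of this, P(X = 0) = 0.97^257 = 0.04%, so nearly all of the 21.5% has at least one control event, and there the adjusted model shows near-certainty.

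**5. Empty HCQ arm with less than complete efficacy** (control rate 3%; the efficacies are assumptions):
- 90% efficacy, HCQ rate 0.3%: 0.997^257 = 46%.
- 80% efficacy, HCQ rate 0.6%: 0.994^257 = 21%.

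**6. Empty HCQ arm with control events, if there is no effect.** With q = (1 - p)^257 the probability is q(1 - q). It is 0.04% at the planned 3%. Rates below 3% are not in the protocol. If they are assumed, the probability is 2% at 1.5%, 7% at 1% and 20% at 0.5%.

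**7. An interval that survives the empty cell.** For 8 v 0 the Wilson limits are 1.59% to 6.02% (8/257) and 0% to 1.47% (0/257). Newcombe's method gives a difference of -3.11 points with limits -3.11 - (6.02 - 3.11) = -6.0 and -3.11 + sqrt(1.47² + (3.11 - 1.59)²) = -1.0.

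**The case against.** The strongest reply is that section 5.i gives the analysis only in general terms and leaves a fuller plan to be developed, which is where a zero-event rule would normally go. That would answer a mere gap. Here the protocol itself names the model, link and covariance estimator, for a group that it sizes on zero events. A later plan can still repair this.

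Three further replies stand, and they limit the point:

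- A reader might infer that the main comparison fails. It does not. The stated comparison is the Fisher test, which is valid at zero events, and nothing lets the adjusted model override it.
- A reader might infer that the relative risk itself breaks down. With no HCQ events and some control events it is 0, reportable as a 100% reduction. Only its log-scale Wald interval is missing, and the protocol does not prescribe a Wald interval for the unadjusted RR.
- At the expected result of about 8 v 0, Fisher also rejects (p = 0.0074). The conclusions then agree in direction, although the adjusted RR and interval remain meaningless.

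The extreme p-values, such as 2e-92, also depend on where the fitting algorithm stops and are not a fixed property of the method. Every tolerance tried gave an absurdly small value. Only one package was used, and another may stop elsewhere or print a warning.

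**Conclusion.** The point holds for the adjusted analysis of the contact group. The named model has no finite estimate on the outcome that the group is sized for, and the robust covariance hides this. If 3% v 0% is exactly true, about 21.5% of trials would pair a non-significant Fisher test with apparent near-certainty from the model. In almost all the others Fisher is significant, but the adjusted RR and interval still mean nothing. If efficacy is assumed to be 90% or 80%, an empty HCQ arm still arises in 46% or 21% of trials.

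A reader might also infer a substantial risk of falsely declaring efficacy. The documents do not support that: with no effect, the route to it has probability 0.04% at the planned 3%, and it reaches 2% to 20% only at assumed attack rates of 1.5% down to 0.5%. Nor do the calculations support a ban on the model at low counts in general. The failure shown is at zero events, and at 8 v 1 the fit is ordinary.

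**What to change.** In section 5.i, for the contact group:

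- Keep the Fisher exact test as the test.
- Report the risk difference with a Newcombe or Miettinen-Nurminen interval alongside the RR.
- State that if either arm has no events, the adjusted analysis replaces robust Poisson with a method that stays finite. Examples are Firth-penalised logistic regression with standardised risks, or a Mantel-Haenszel risk difference by site. Choose one before the data are seen.

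This costs a few lines of analysis text and one extra effect measure to report. The sample size and the unadjusted test do not change.

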## 6. Benefit/risk assessment

Infection with SARS-CoV-2 can be unpredictable in its severity, but a 3.4% mortality rate has been observed among clinical pneumonia cases. The elderly (>60 years) and those with medical co-morbidities are at highest risk of poor outcomes (29). Pregnant women are one of the vulnerable groups for this infection with increased severity of the disease if they become infected (3,12). The efficacy of HCQ in preventing the infection and reducing the severity of the disease is very limited and therefore, there is equipoise as to whether the *in vitro* efficacy of HCQ will translate into preventive efficacy from disease or even a reduction in viral shedding. On the other hand, the safety of HCQ in pregnancy is well established in pregnancy. Thus, the potential benefit-to-risk ratio for testing HCQ in pregnant women is favourable.

## 7. Ethical considerations

The project will be carried out with the highest standards of research integrity set out in the European Code of Conduct for Research Integrity and in total agreement with the applicable international, EU and Spanish national law.

Sampling of humans will always be made under The Nuremberg Code (1947) addressing volunteer consent and proper acting, the Revised Declaration of Helsinki and the convention for the protection of human rights and dignity of human beings with regard to the application of biology and medicine called the "Convention on Human Rights and Biomedicine" (Council of Europe, Oviedo, 1997) and its additional protocol on biomedical research (2005). All samples and databases will be anonymized.

In agreement with this, the ethical issues encountered are addressed in detail below.

### a. Human participants involved

The COVID-Preg study is designed to respond to the urgent questions related to finding effective preventive interventions to reduce the risk and consequences of SARS-CoV-2 infection in pregnant women and their infants. This is needed for increasing the effectiveness of preventive tools and improving clinical management, allowing women to make informed health decisions. A fundamental ethical requirement in any clinical research is that the participants are those least vulnerable, in this case it would pregnant women; however, scientific evidence shows that efficacy and safety findings from COVID-19 control strategies evaluated in non- pregnant adults cannot be directly extrapolated to pregnant women. Pregnant women require specifically tailored interventions including those related to COVID-19 control.

Both oral and written communication will be used to provide information to pregnant women who are invited and interested in participating in the study. If a woman meeting inclusion criteria is interested in participating, she will be informed about the objectives and procedures of the study and about the risks and benefits of enrolling herself in the study. Ample time, adapted to each woman needs, will be given for consideration of the consent forms, and any questions will be responded by the investigator before the consent is signed.

### b. Informed consent

Informed consent is a process that is initiated prior to the individual's agreeing to participate in the study and continuing throughout the individual's study participation. The informed consent will be sent for approval to the Institutional Review Board (IRB) and the participants will be asked to read and review the document.

The consent form for the clinical trial (Annex 4) has been designed to provide information on the following aspects: general COVID-19 education, information about individual's rights as a study participant, what biological samples will be collected, the use of these samples, the

schedule of follow-up visits, confidentiality of personal data collected and potential risks and benefits of the study. It also specifies that participants have the right to leave the study whenever they decide and that this will not affect the clinical care that the patient will receive thereafter. The consent form is thorough but understandable by a lay person.

Three identical copies of the consent form will be signed. Two of the copies will be provided to the volunteer (one to be forwarded to the health system worker responsible for the control of her pregnancy) and the other copy will be kept in the study file by the site investigator.

